**Stage 1 (Sessions 1 to 7): Introduction and Psychoeducation**
Engage the participant in the program and in the process of change.Provide relevant psychoeducation about obesity, weight loss, and eating disorders.Provide initial education about nutrition and physical activity.Introduce proactive problem-solving techniques.Explain the difference between healthy versus disordered eating and exercise habits.

**Stage 2 (Session 8 to 26): Core Interventions**
Address changes in eating related to events and mood.Encourage participants to improve their interpersonal functioning and fortify their supportive relationships.Guide participants through mindfulness and relaxation exercises.Address dissatisfaction with body image and weight.Address unhealthy body checking, comparison, and avoidance.Encourage participants to engage in self-nurturing activities.Improve participants’ knowledge regarding nutrition and physical activity and motivate participants to continue engagement with behavioural weight loss strategies.Help participants to identify any existing or emerging barriers to change.Help participants to personalize their HAPIFED formulation and adjust interventions according to their individualized formulation.Use cognitive therapy and behavioural experiments in order to help participants to restructure any unhelpful thinking styles they may have and reduce their disordered eating behaviours.Encourage participants to engage in activities that enhance positive self-evaluation and are not related to shape, weight, or eating.

**Stage 3 (Sessions 27 to 30): Relapse Prevention**
Help participants to think about strategies to maintain healthy eating and healthy physical activity levels after program completion.Encourage the maintenance of any improvements in eating disorder symptoms.Help participants to develop a detailed post-program management plan.

### 2.4. Study Intervention

The intervention under study is the HAPIFED program; however, it is not being provided as part of the current study. Rather, HAPIFED is being provided by the therapist delivering the program as part of their practice. Data will be collected using online questionnaires, from individuals who are undertaking the HAPIFED program as part of their prescribed healthcare, as well as from their therapists.

### 2.5. Duration

The total duration of the study is 156 weeks (36 months). Participants will take part in the HAPIFED program for up to 30 weeks (approximately 7 months), and data will continue to be collected for a total of 156 weeks (36 months) from commencement of therapy, to determine long-term effectiveness (Table 1).

### 2.6. Study Participants and Eligibility Criteria

Individuals with overweight or obesity who identify as having disordered binge eating behaviours that are characteristic of binge eating disorder, bulimia nervosa, or OSFED with recurrent binge eating, will be eligible for the study.

#### 2.6.1. Inclusion Criteria

Male or female aged 18 years and over;Able to read, write and communicate in English and be willing to provide written, informed consent;A BMI of ≥25 kg/m^2^. This criterion includes individuals with obesity (BMI ≥ 30 kg/m^2^), as well as those with a BMI in the overweight range (25–29.9 kg/m^2^). A BMI of ≥25 kg/m^2^ is associated with an increased risk of disease [34,35]. Weight loss offers numerous health benefits to such individuals [37,38,43,44,45,47,48,49,50,52,53,54,55] and may indeed serve as a preventative measure in ensuring that an individual’s weight trajectory does not increase from the overweight to the obese range, as is often seen in those with binge eating disorder [59]. Individuals with a BMI of ≥25 kg/m^2^ often want and seek to lose weight [9,24]. It is therefore appropriate to allow such individuals to enter the study if they wish;A global score on the EDE-Q that is greater than 1 standard deviation (1.25) above the Australian community norm of 1.52 (i.e., above 2.77) [60];Willing to undertake the HAPIFED program of up to 30 weeks (approximately 7 months) in duration involving behavioural weight loss therapy and CBT-E, and to attend sessions regularly (i.e., not miss more than 3 sessions over the course of the program);Have access to a computer, the Internet and an e-mail account and be willing to complete the online questionnaires up to 156 weeks (36 months) from study entry.

#### 2.6.2. Exclusion Criteria

Pregnant or breast-feeding, or having a desire to become pregnant during the first 52 weeks of the study;Receiving current treatment with a weight loss medication such as, but not limited to, orlistat, phentermine, or liraglutide, or other medication which is known to cause weight loss such as topiramate or lisdexamfetamine, or have received treatment with such medication in the 5 weeks prior to screening, taking into consideration the half-life and subsequent washout period of the medication. The reason for this is to ensure that weight loss as a result of the medication does not contribute to any weight loss during study participation. An additional reason for this exclusion criterion is that the EDE-Q asks about eating behaviour in the previous 4 weeks, and an individual’s responses to the EDE-Q may not be an accurate reflection of their usual behaviour if they have been taking weight loss medication in that time period;Undergone bariatric surgery or intragastric balloon insertion in the 24 months prior to screening, due to the fact that weight loss may continue for up to 24 months post-procedure [61,62];Greater than 3 kg weight change in the 5 weeks preceding screening, to ensure that participants are relatively weight-stable at study entry so that any weight change throughout the study may be confidently attributed to the HAPIFED program without uncertainty that it may be influenced by prior weight changes;Diagnosis of a clinical condition, or use of a medical treatment, that interferes with appetite regulation (e.g., Prader–Willi or Cushing’s syndrome, or some steroid treatments). The reason for this criterion is that the behavioural weight loss intervention in HAPIFED requires participants to eat according to appetite, but this is likely to result in weight gain for people with conditions or who are using treatments that stimulate appetite.

### 2.7. Study Procedures and Data Collection

#### 2.7.1. Screening/Baseline

Potential participants will be informed of the study by the HAPIFED therapist and provided with a copy of the study brochure listing the selection criteria and instructions on how to take part in the study and complete the online questionnaires. Interested participants will be directed to a secure online webpage that contains the ‘Information for Participants,’ an online screening questionnaire, and a consent form.

Following consent, participants will complete the online baseline questionnaires. There will be no time limit for completion of the online questionnaires; however, it is expected to take approximately 40 min and will include the following components: Height;Weight;Demographic Questionnaire: gender, marital status, ethnicity, occupation, education;Commonwealth Scientific and Industrial Research Organisation (CSIRO) Healthy Diet Score Survey [63];Eating Disorder Examination Questionnaire (EDE-Q) [64,65];Depression, Anxiety, and Stress Scale with 21 Items (DASS-21) [66];Short-Form Health Survey with 12 Items, Version 2 (SF-12v2) [67];Cost-Effectiveness questionnaire, which includes information about medication use (current medication including name of drug, total daily dose, dosing frequency, and indication).

#### 2.7.2. Follow-Up

Participants will be followed up at 30 weeks (approximately 7 months) after commencement of the HAPIFED program, by which stage it is expected to be completed, and then at 52 weeks (12 months), 104 weeks (24 months), and 156 weeks (36 months), following commencement of the program to determine long-term effectiveness (Table 1). As for the baseline questionnaires, participants will be sent an e-mail with instructions and an embedded web link to complete the same online questionnaires as completed at baseline, but without the question about height or the Demographic Questionnaire. They will also be required to complete the Client Satisfaction Questionnaire (CSQ-8) [68] and the Process Evaluation Questionnaire for Participants at week 30 (month 7).

All nonrespondents will be identified and sent up to two reminder emails for each data collection time point.

### 2.8. Outcome Measures

#### 2.8.1. Primary Outcomes

The co-primary outcomes are as follows:(1)The proportion of participants that have lost ≥5% of their baseline body weight at 52 weeks (12 months) after program commencement.(2)The proportion of participants that have a global score on the EDE-Q that is less than 1 standard deviation (1.25) above the Australian community norm of 1.52 (i.e., below 2.77) [60] at 52 weeks (12 months) after program commencement.

Weight loss of ≥5% of body weight is considered clinically significant [69] and is associated with a reduction in the risk of noncommunicable diseases as well as with improvements in overall health and quality of life [43,70,71]. Indeed, the Australian Government’s Therapeutic Goods Administration uses this level as a threshold for evidence of weight loss efficacy for weight loss medications.

The EDE-Q is a widely used and validated self-report version of the diagnostic, interview-based Eating Disorder Examination [72]. This questionnaire will provide a comprehensive assessment of the range and severity of eating disorder psychopathology. The rationale for using the outcome measure of a global score on the EDE-Q that is less than 1 standard deviation above community norms is for the purpose of comparison with previous studies involving CBT-E [22,73,74]. A reduction in the global score on the EDE-Q to a value that is less than 1 standard deviation above community norms is considered a good outcome or ‘remission’ [22], and indeed, the majority of studies conducted with CBT-E used this threshold as a measure of efficacy [22,73,74].

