### 2.2. Study Design

This will be a prospective study of the real-world effectiveness of the HAPIFED program for the treatment of individuals with overweight or obesity and who identify as having comorbid disordered binge eating behaviours that are characteristic of comorbid binge eating disorder, bulimia nervosa, or OSFED with recurrent binge eating.

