### 2.10. Sample Size

Based on the Australian government’s recommendation for obesity treatments that at least 50% of participants in a treatment group must achieve a weight loss of at least 5% of initial body weight to demonstrate a clinically significant benefit [69], and the HAPIFED pilot results where 50% of the sample had an EDE-Q score of less than one standard deviation (1.25) above the community normative score of 1.52 (i.e., below 2.77) [56,60] at the end of treatment (whereas all had a score above 2.77 before treatment), we estimated that a sample size of at least 164 participants (with 5% significance level and power of 80%) is required. To allow for an up to 50% attrition rate as that found in the pilot study [56], we inflated the sample size to 246 to ensure complete data. 

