## Figures and Tables

**Table 1 behavsci-09-00072-t001:** Schedule of Assessments.

	ASSESSMENT	SCREENING/BASELINE	WEEK 30 (MONTH 7)	WEEK 52 (MONTH 12)	WEEK 104 (MONTH 24)	WEEK 156 (MONTH 36)
		WEEK 0 (MONTH 0)				
Conducted by Participants (online)	Screening/Eligibility	✓				
	Written Informed Consent	✓				
	Height	✓				
	Weight	✓	✓	✓	✓	✓
	Demographic Questionnaire	✓				
	CSIRO * Healthy Diet Score Survey	✓	✓	✓	✓	✓
	Eating Disorder Examination Questionnaire (EDE-Q)	✓	✓	✓	✓	✓
	Depression, Anxiety and Stress Scale with 21 Items (DASS-21)	✓	✓	✓	✓	✓
	Short-Form Health Survey with 12 Items, Version 2 (SF-12v2)	✓	✓	✓	✓	✓
	Cost-Effectiveness Questionnaire	✓	✓	✓	✓	✓
	Client Satisfaction Questionnaire (CSQ-8)		✓			
	Process Evaluation Questionnaire for Participants		✓			
Conducted by Therapists (online)	Process Evaluation Questionnaire for Therapists		✓			

* CSIRO, Commonwealth Scientific and Industrial Research Organisation.

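### The EDE-Q co-primary counts success at the same 2.77 cut that defines entry, so some week-52 remissions are expected from regression to the mean alone and a difference from 0% is not evidence of benefit

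*Protocol article*

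**What the plan says.** - **Entry.** Section 2.6.1 requires "A global score on the EDE-Q that is greater than 1 standard deviation (1.25) above the Australian community norm of 1.52 (i.e., above 2.77").
- **Success.** Section 2.8.1 counts a "global score on the EDE-Q that is less than 1 standard deviation (1.25) above the Australian community norm of 1.52 (i.e., below 2.77"), assessed once, "at 52 weeks (12 months) after program commencement". No minimum fall is required. The section justifies the cut by comparability with earlier CBT-E studies.
- **Pre-treatment measurement.** Table 1 has one merged "SCREENING/BASELINE" column with one EDE-Q entry. Section 2.7.1 lists the EDE-Q only among the questionnaires completed after consent: "Following consent, participants will complete the online baseline questionnaires".
- **Design.** Section 2.2: "This will be a prospective study of the real-world effectiveness of the HAPIFED program". No control group is described.
- **Analysis.** Section 2.11 assigns McNemar's test to categorical data, and repeated-measures logistic regression with covariates to dichotomous outcomes.
- **Sample size.** Section 2.10 takes 50% as the pilot success rate at the end of treatment, "whereas all had a score above 2.77 before treatment".

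**The concern.** Selecting people because a fluctuating score lies above a line, and then counting how many later lie below it, yields a non-zero count whenever the two scores are less than perfectly correlated. Someone who enters at 2.80 and scores 2.75 a year later is a success. Nobody can move the other way, because everyone starts as a failure. With no comparator and no second pre-treatment score, nothing in the design shows how many crossings would have occurred anyway.

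The protocol guards against the analogous problem for its other co-primary: section 2.6.2 excludes people whose weight changed by more than 3 kg in the five weeks before screening. The EDE-Q has no matching safeguard.

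At stake is how the co-primary is read. If any difference from 0% is taken as evidence of effectiveness, an inert programme can pass.

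**Working it through.** **1. The cut.** 1.52 + 1.25 = 2.77. The plan's figure reproduces, and it is the same for entry and success.

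**2. Inputs.** From the documents: cut 2.77; N = 246; attrition up to 50%, which leaves 246 × 0.5 = 123 at week 52; stated requirement of 164. Not in the documents, so assumed: mean 3.0 to 4.0 and SD 1.0 among people presenting, and a 12-month correlation r of 0.9 to 0.6. In this model r below 1 covers both measurement error and natural fluctuation over the year.

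**3. Crossings with no effect.** X1 (entry) and X2 (week 52) are bivariate normal with equal means and SDs. The null rate is P(X2 < 2.77 | X1 > 2.77).

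| Mean | r = 0.9 | r = 0.8 | r = 0.7 | r = 0.6 |
|---|---|---|---|---|
| 3.0 | 11.8% | 16.9% | 20.8% | 24.3% |
| 3.5 | 7.1% | 10.1% | 12.5% | 14.4% |
| 4.0 | 3.7% | 5.3% | 6.4% | 7.3% |

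Among 123 responders this runs from 0.037 × 123 ≈ 5 to 0.243 × 123 ≈ 30 remissions. Raising the SD to 1.25 at mean 3.5 changes the row to 8.4%, 11.9%, 14.7% and 17.0%.

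**4. What a test against 0% does with this.** If all b discordant pairs go one way, the exact two-sided McNemar p-value is 2 × 0.5^b. For b = 5 it is 0.0625; for b = 6 it is 0.031. So six remissions reach significance at any sample size.

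**5. Chance of at least six under no effect.** For null rate q, this is 1 − Σ C(n,k) q^k (1 − q)^(n−k), summed over k = 0 to 5.

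| q | n = 123 | n = 164 | n = 246 |
|---|---|---|---|
| 3.7% | 30% | 57% | 90% |
| 5% | 58% | 83% | 99% |
| 7% | 87% | 98% | over 99% |

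The nominal level is 5%.

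**6. Adding a reliable-change condition.** Count a remission only if X2 < 2.77 and X1 − X2 > 1.96 × SD × √(2(1 − r)). At SD 1.0 the bound is 0.88, 1.24, 1.52 and 1.75 for r = 0.9, 0.8, 0.7 and 0.6. At mean 3.5 the null rate becomes 1.0%, 1.4%, 1.7% and 2.0%, against 7.1% to 14.4% without the condition.

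This gain depends on using the 12-month r in the bound. If the bound is built on 0.9 (0.88 points) while the 12-month correlation is really 0.7, the null rate at mean 3.5 is 6.5%.

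**The case against.** - **The cut has a stated purpose.** Comparability with CBT-E studies is a good reason to report it, and that stands. It does not make a comparison with 0% informative.
- **The test against 0% is not spelled out.** This stands. The co-primary is defined as a proportion at week 52, and section 2.11 names logistic regression for dichotomous outcomes as well as McNemar's test for categorical data. A McNemar test against baseline is the likely reading, not an explicit one. The point applies to any before-after test against 0%.
- **The single measurement is inferred.** Section 2.7.1 mentions an online screening questionnaire without giving its content. If that held a separate EDE-Q, this part would weaken. Table 1 shows only one.
- **The size rests on assumptions.** It does. A reader might infer that an inert programme would certainly reach significance. The mildest case above gives only a 30% chance with 123 responders, so the supported word is *can*.
- **Regression to the mean might be thought to explain the pilot's 50%.** It does not under these assumptions, which give at most about 24%. A week-52 result near 50% would stand clear of that range.
- **The attribution wording.** Section 2.6.2 says that "any weight change throughout the study may be confidently attributed to the HAPIFED program". A reader might take this as a causal claim about the EDE-Q. It concerns weight only and explains the weight-stability criterion, so rewording it would not cure this problem.
- **Other outcomes help.** Change in EDE-Q severity is a secondary outcome and would reveal trivial crossings, but a mean change from the same selected baseline also carries regression to the mean.

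**Conclusion.** The concern holds as a limit on interpretation. The shared cut, the 0% starting rate and the absence of a comparator follow from the text; the single pre-treatment EDE-Q follows from Table 1. Some remissions must therefore be expected without any effect. How many cannot be derived from the protocol: under the assumptions stated, about 4% to 24% of entrants, and 7% to 14% at mean 3.5. That is less than the 50% the sponsor anticipates, but it can suffice for significance against 0%. The documents do not support the stronger conclusions that a null programme is bound to succeed or that a high remission rate would be uninterpretable.

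**What to change.** 1. Keep the 2.77 cut so that results remain comparable with the CBT-E studies.
2. Report the week-52 proportion with a 95% CI, and state that a difference from 0% will not be taken as evidence of benefit. Compare the lower confidence limit with a non-zero no-treatment benchmark, fixed in advance and justified by the sponsor. The documents supply no such value, and none is proposed here.
3. Pre-specify a companion analysis that counts remission only if the score is below 2.77 and the fall from baseline exceeds a reliable-change bound, for example 1.96 × SD × √(2(1 − r)). State the source of the SD and r, and prefer an r that reflects the 12-month interval.

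This needs analysis-plan wording and one further calculation on data already scheduled, with no added burden on participants. The downside is a somewhat less favourable headline figure.

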#### 2.8.2. Secondary Outcomes

The secondary outcomes are the change in the following parameters between baseline and follow-up at week 30 (approximately 7 months) and at 12, 24, and 36 months:Anthropometric parameters:○absolute weight;○weight as a percentage of baseline body weight;○BMI;○the proportion of participants who achieve ≥5% loss of baseline body weight;○the difference in the effect of HAPIFED on anthropometric parameters for people with different classifications of overweight or obesity at baseline (Overweight = BMI of 25–29.9 kg/m^2^; Class 1 Obesity = BMI of 30–34.9 kg/m^2^; Class 2 Obesity = BMI of 35–39.9 kg/m^2^; Class 3 Obesity = BMI of ≥40 kg/m^2^) [75]; Eating disorder parameters:
○severity of the eating disorder, as assessed using the EDE-Q [65,72]; Dietary parameters:
○nutritional quality of food choices, including the intake of fruit and vegetables, as assessed using the CSIRO Healthy Diet Score Survey [63]. The CSIRO Healthy Diet Score Survey is a scientifically validated survey that assesses an individual’s diet against Australia’s healthy eating guidelines [76]; Psychosocial parameters:
○depression, anxiety, and stress, as assessed using the DASS-21 [66]. The DASS-21 is a self-report scale with 21 items used to assess symptoms of depression, anxiety and stress;Quality of life as assessed using the SF-12v2 [67]. The SF-12v2 is a self-report scale with 12 items used to assess mental and physical functioning and overall health-related quality of life;Economic parameters:
○cost-effectiveness of the HAPIFED program as assessed by the use of a questionnaire to determine health-care utilization, medication use, and days off work.

### 2.9. Process Evaluation

Participants and therapists will be asked to complete an online Process Evaluation Questionnaire at the completion of the program (Table 1). 

The Process Evaluation Questionnaires will be used to collect information on the implementation and acceptability of the program to both the participant and the therapist. This information will be used in conjunction with the CSQ-8 [68] to evaluate the HAPIFED program in clinical practice, and to inform strategies to enhance translation of the findings from this study into wider-scale clinical practice. 

### 2.10. Sample Size

Based on the Australian government’s recommendation for obesity treatments that at least 50% of participants in a treatment group must achieve a weight loss of at least 5% of initial body weight to demonstrate a clinically significant benefit [69], and the HAPIFED pilot results where 50% of the sample had an EDE-Q score of less than one standard deviation (1.25) above the community normative score of 1.52 (i.e., below 2.77) [56,60] at the end of treatment (whereas all had a score above 2.77 before treatment), we estimated that a sample size of at least 164 participants (with 5% significance level and power of 80%) is required. To allow for an up to 50% attrition rate as that found in the pilot study [56], we inflated the sample size to 246 to ensure complete data. 

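### The allowance for 50% attrition multiplies by 1.5 instead of dividing by 0.5, so 246 enrolled leaves 123 with data, not the required 164

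*Protocol article*

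**What the plan says.** Everything relevant is in section 2.10 (Sample Size) of the protocol article.

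- The base requirement: "we estimated that a sample size of at least 164 participants (with 5% significance level and power of 80%) is required".
- The allowance for loss: "To allow for an up to 50% attrition rate as that found in the pilot study [56], we inflated the sample size to 246".
- The resulting target and its purpose: "we inflated the sample size to 246 to ensure complete data".

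Read together, 164 is the number needed with outcome data, and 246 is the enrolment meant to deliver that number after losses of up to half. No other section gives a different attrition rate or another basis for 246.

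**The concern.** If the base number is to survive a loss of a given fraction, enrolment must equal the base number divided by the fraction that remains. Increasing the base by the attrition percentage is a different operation, and it always gives too few. The gap is small when attrition is low and large at 50%.

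The 80% power claim is made for the trial as planned, and both co-primary outcomes (section 2.8.1) depend on it. They are measured at 52 weeks, some 22 weeks after the 30-week assessment, by online questionnaires with up to two e-mail reminders per time point (section 2.7.2). Heavy loss is therefore a realistic prospect. If it reaches the rate that the plan itself cites, the study falls well short of its stated requirement. A null or imprecise result could then be read as coming from an adequately powered study.

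**Working it through.** **Inputs, all from section 2.10:** required number with data, n = 164; attrition, d = up to 0.50; enrolment target, N = 246; significance level 5% (sidedness not stated); power 80%.

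**1. Reproducing the plan's figure.** n × (1 + d) = 164 × 1.5 = 246. This matches exactly, so this is how the target arises numerically.

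**2. What 246 delivers at the stated attrition.** N × (1 − d) = 246 × 0.5 = 123. The shortfall is 164 − 123 = 41, and 41/164 = 25%.

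**3. The enrolment that matches the stated aim.** n / (1 − d) = 164 / 0.5 = 328, which is 328 − 246 = 82 more than planned.

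**4. The attrition that 246 can absorb.** 1 − 164/246 = 0.333. Above one third, fewer than 164 remain.

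**5. Effect on power.** The article gives no comparison proportion, test or sidedness, so 164 cannot be rebuilt. Power at a smaller number can still be obtained without knowing the effect, by taking the plan's statement that 164 gives 80% and scaling the noncentrality by the square root of the ratio of sample sizes:

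Power at m = Φ[(z_α + 0.842) × √(m/164) − z_α]

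- Two-sided 5%, m = 123: Φ[(1.960 + 0.842) × √0.75 − 1.960] = Φ(0.467) = 0.68.
- One-sided 5%, m = 123: Φ[(1.645 + 0.842) × √0.75 − 1.645] = Φ(0.509) = 0.69.

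As a cross-check, take a one-sample test of a proportion against 0.50 (an assumption), with the alternative solved so that 164 gives 80% power. The alternative is about 0.61 two-sided or 0.60 one-sided, and power at 123 is then 0.677 or 0.693. The two routes agree.

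**6. Effect on precision, for illustration.** The 95% half-width around an observed 50% is 1.96 × √(0.25/m): 7.7 percentage points at 164 and 8.8 at 123. The article sets no precision target.

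| Attrition with 246 enrolled | Number with data | Power if 164 gives 80% (two-sided) |
|---|---|---|
| 33.3% | 246 × 0.667 = 164 | 0.80 |
| 40% | 246 × 0.60 = 147.6 | Φ(2.802 × √0.90 − 1.960) = 0.76 |
| 50% | 246 × 0.50 = 123 | 0.68 |

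**The case against.** The arithmetic is hard to dispute. The case on the other side concerns how much follows from it.

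*Fifty per cent is a ceiling.* The article allows for attrition up to that rate, and below one third 246 is enough. This stands as a limit on the claim: the shortfall begins above 33.3% and reaches 41 at the ceiling. It does not rescue the sentence, because an allowance stated to cover losses up to 50% has to hold at 50%, and that is the rate reported from the pilot.

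*Attrition may mean leaving the program, not missing outcomes.* Questionnaires are e-mailed at fixed times from program commencement. Section 2.11 plans an intention-to-treat analysis of the complete cohort and compares outcomes between completers and noncompleters, so people who stop the program may still supply data. That is possible, and the pilot report is not available to settle it. But section 2.10 itself ties the inflation to having complete data. If those who leave were all expected to supply outcomes, no inflation would have been needed.

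*The 68% is not anchored in a stated test.* This is fair. The only test that section 2.11 names for categorical data is McNemar's. Every participant must score above 2.77 on the EDE-Q at entry, and nobody can have lost 5% of baseline weight at baseline. Against that baseline, with about half responding, power would be close to 100% at 123 and at 164 alike. The 68% is therefore conditional on the plan's own claim that 164 gives 80%. If that claim does not describe the intended test, the power statement has a separate difficulty, but the inflation is still wrong.

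**Conclusion.** The concern holds. The enrolment target does not do what section 2.10 says it does. At the stated 50% attrition it leaves 123 participants with data instead of 164, a deficit of 25%. The matching enrolment is 328, and 246 tolerates attrition of at most one third.

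These counts rest only on figures printed in that section and on reading attrition as loss of outcome data, which is the reading the section supports. The fall in power from 80% to about 68% (two-sided) or 69% (one-sided) rests on one further assumption: that 164 gives exactly 80%, as stated. Because the printed figures contradict one another, detail held in a fuller protocol or analysis plan could not reconcile them.

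**What to change.** Correct the sentence on attrition in section 2.10 in one of two ways.

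1. **Keep 246 and describe it accurately.** State that 164 participants with data are retained only if attrition is 33% or less, and that at the pilot's 50% attrition 123 would remain. If a power figure is added, give it as conditional: about 68% (two-sided) for the effect that 164 would detect with 80% power. The half-width of 8.8 percentage points around 50% can be given alongside.
2. **State 328** as the enrolment that leaves 164 at 50% attrition.

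The first option is sufficient. It costs one corrected sentence, needs no additional enrolment and leaves design, outcomes and analysis unchanged. Its price is a less favourable statement of power. The second would mean enrolling 82 more people than now planned.
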